### **2.2. Specific Objectives**

- 1 To determine prevalence and distribution of dental caries, periodontal conditions and oral impacts on daily performance among adolescents in Copperbelt Province, Zambia
- 2 To determine the association between dental caries and oral health related quality of life among adolescents in Copperbelt Province
- 3 To assess the effects of a six months modified basic package of oral care intervention on knowledge and behaviors related to dental caries after 18 and 24 months of follow up.
- 4 To assess the effects of a six months modified basic package of oral care intervention on prevalence of dental caries after 18 and 24 months of follow up
- 5 To assess the effects of a six months modified basic package of oral care intervention on prevalence of oral impacts on daily performance after 18 and 24 months of follow up

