#### **4.6. The trial intervention**

The trial intervention is a modified WHO –BPOC which include all the 3 packages of BPOC plus oral health education. The first package, Oral Urgent Treatment (OUT) will include simple extraction of teeth beyond restorable condition and referral for teeth requiring clinic set up for removal. The second package which is Atraumatic Restorative Treatment (ART) will be executed using hand instruments only by removing decayed part of teeth with cavities not reaching the pulp or not diagnosed as irreversible pulpitis then filling with Fuji IX Glass- ionomer. The third component (Affordable Fluoridated Tooth pastes) will be done by providing 250g pack of fluoride toothpaste every two months and toothbrushes every three months for 18 months. In addition to WHO-BPOC the study will also give peer provided oral health education. The peer educators will be furnished with the following printed messages to deliver to their classmates in the intervention groups once after every two weeks for a period of 18 months;

1. Restrict the frequency of taking sugary food and drinks in the diet to less than five times per day.
2. Brush your teeth for 2 minutes ensuring all the surfaces are cleaned; twice per day in the morning and evening before retiring to bed.
3. Use fluoride toothpaste to brush, spit the foam but do not rinse it out.
4. Change your toothbrush every 3 months or when bristles flare out.
5. Advise your parent or guardian to buy a tooth paste containing at least 1450 ppm fluoride and to take you for dental check up at least once a year.

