#### **4.10. Study outcomes**

The expected primary outcomes are improved oral health (dental caries status and gingivitis) and OHRQoL. The secondary outcomes include improved oral hygiene (plaque score) and oral health knowledge and related behaviors. The effect sizes for improvement in oral health and oral health related quality of life are based on average improvement achieved in similar studies reviewed.

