## Part 2 Adolescents oral health knowledge and behaviors

16. I can avoid tooth decay by accomplishing the following;

- |                                                                                                                                              | 1=yes                    | 2=no                     |
|----------------------------------------------------------------------------------------------------------------------------------------------|--------------------------|--------------------------|
| 1. Restricting eating of sugar containing foods such as vitumbua, filters, cake, chocolate to less than five times per day                   |  |  |
| 2 Restricting drinking of sugar sweetened drinks such as tea, coffee, porridge, coke, fanta, mukoyo or juice to less than five times per day |  |  |
| 3. Using fluoride toothpaste to brush my teeth at least twice a day spitting the foam but not rinsing it out                                 |  |  |
| 4 Visiting a dentist at least once a year for dental check up                                                                                |  |  |

17. I can avoid bleeding gums by fulfilling the following;

- |                                                                                                 | 1=yes                    | 2=no                     |
|-------------------------------------------------------------------------------------------------|--------------------------|--------------------------|
| 1. Restricting eating/drinking of sugar containing foods/ drinksto less than five times per day |  |  |
| 2. Brushing teeth for 2 minutes at least twice a day                                            |  |  |
| 3. Visiting a dentist at least once a year for dental check up                                  |  |  |
| 4 Using a dental floss to clean between my teeth                                                |  |  |
| 5 Using a tooth pick to clean between my teeth                                                  |  |  |

18. When should a tooth brush be changed

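### The only tooth-decay knowledge question has 'yes' as the taught answer to all four items, so it cannot separate knowing from agreeing, and the bias in the arm comparison can go either way

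*Protocol*

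**What the plan says.** Protocol section 2.2, Objective 3, asks for the effect of the intervention on "knowledge and behaviors related to dental caries after 18 and 24 months of follow up". Section 4.10 makes knowledge a secondary outcome: "The secondary outcomes include improved oral hygiene (plaque score) and oral health knowledge and related behaviors".

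The instrument is printed in Appendix 1. In Part 2, question 16 opens with "I can avoid tooth decay by accomplishing the following" and lists four statements, each with only a yes box and a no box:

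- 16.1: "Restricting eating of sugar containing foods such as vitumbua, filters, cake, chocolate to less than five times per day"
- 16.2: "Restricting drinking of sugar sweetened drinks such as tea, coffee, porridge, coke, fanta, mukoyo or juice to less than five times per day"
- 16.3: "Using fluoride toothpaste to brush my teeth at least twice a day spitting the foam but not rinsing it out"
- 16.4: "Visiting a dentist at least once a year for dental check up"

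The other two knowledge blocks cover other topics: question 17 asks about bleeding gums and question 18 about when to change a toothbrush. Section 4.6 lists the messages that peer educators deliver in the intervention arm, the first being "Restrict the frequency of taking sugary food and drinks in the diet to less than five times per day". Table 1 gives 36 such sessions. Section 4.9.2 (Blinding) says that pupils in the intervention group will know their group. The Protocol states no scoring rule for knowledge.

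**The concern.** A knowledge item is informative only if a pupil who does not know can be seen not to know. In question 16 agreement alone produces the taught answer every time. The recorded 'yes' mixes three kinds of pupil: those who know, those who guess, and those who agree with whatever is put to them.

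The between-arm comparison then rests partly on how often uninformed pupils agree in each arm, and the form does not measure this for tooth decay. No later scoring rule or model can recover it, because the contrasting items were never asked. What is at stake is the interpretation of one secondary outcome. Caries, gingivitis and oral-health-related quality of life are not affected.

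**Working it through.** The Protocol gives no figure for this point, so there is none to reproduce. The check has two parts.

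**1. The answer key.** Each item set against the taught messages in section 4.6:

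| Item | Taught message | Answer in line with it |
|---|---|---|
| 16.1 sugary foods | 1 | yes |
| 16.2 sugary drinks | 1 | yes |
| 16.3 fluoride paste, twice daily, no rinsing | 2 and 3 | yes |
| 16.4 yearly check-up | 5 | yes |

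All four are keyed 'yes'. A pupil with no knowledge who ticks 'yes' throughout agrees with the key on 4 of 4. One who ticks at random agrees on 2 of 4 on average, and on all four with probability 0.5⁴ = 6%. If the chance of a 'yes' is 0.8, that probability is 0.8⁴ = 41%.

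**2. Effect on the arm comparison.** Let k be the true share who know an item, and g the chance that a pupil who does not know ticks 'yes'. Then

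observed share = k + (1 − k)g.

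All values of k and g below are assumptions.

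*Equal g in both arms.* The observed difference is (k₁ − k₀)(1 − g). With k₀ = 0.40 and k₁ = 0.70 (30 points, odds ratio 3.5):

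- g = 0.5: 0.40 + 0.60 × 0.5 = 70%, and 0.70 + 0.30 × 0.5 = 85%. Difference 15 points, odds ratio 2.43.
- g = 0.8: 0.40 + 0.60 × 0.8 = 88%, and 0.70 + 0.30 × 0.8 = 94%. Difference 6 points, odds ratio 2.14.

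*g higher in the taught arm, no true difference.* With k = 0.40 in both arms, g = 0.5 in control and 0.8 in intervention:

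- control: 0.40 + 0.60 × 0.5 = 70%
- intervention: 0.40 + 0.60 × 0.8 = 88%

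This is an 18-point gain with no gain in knowledge.

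*Illustrative power under equal g.* Section 4.4 gives 1600 pupils before the allowance for loss and a design effect of 1 + (80 − 1) × 0.01 = 1.79. That is 800 / 1.79 = 447 effective pupils per arm. The lower end of the African range that section 3.0 reports for knowledge of sugar as a cause of decay is 48.2%. For an assumed true rise from 48.2% to 58.2%, power at the two-sided 5% level is about 0.85 at g = 0, 0.42 at g = 0.5 and 0.21 at g = 0.75. For the larger 40% to 70% gain, power is still about 88% at g = 0.8.

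**The case against.** The strongest objection is to any claim about direction. A reader might infer that the knowledge effect must be compressed. That needs equal yes-saying in both arms, and the documents give reason to doubt it: intervention pupils know their group and hear the same messages in 36 sessions. The objection stands. The bias may shrink the effect or create one.

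Two further inferences are tempting and should not be drawn.

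- That the 'I don't know' in question 18 shows its absence from question 16 to be an oversight. Question 17 uses the same yes/no grid without it, and in question 18 it is a separate row, not a third answer to each item.
- That partial knowledge on 16.3 scores the same as full knowledge. This is so only if the partly informed pupil ticks 'yes'. One who knows about fluoride but thinks that rinsing is right may tick 'no'.

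It can also be said that no total score is defined and that scoring may properly be left to an analysis plan. That is true, and item-by-item reporting would fit Appendix 6 equally well. But each item alone has the same defect, and an analysis plan cannot supply answers that were not collected. Section 4.11.3 says that the questions come from standardized instruments; nothing there shows that this block was tested for agreement bias.

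Finally, a pupil who ticks 'yes' throughout would contradict himself or herself in question 18, and the tooth-pick item in question 17 matches no taught message. These give some sight of uniform yes-saying on the form as a whole, but no such check is planned and neither item concerns tooth decay.

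**Conclusion.** The point holds as a defect of one block of the questionnaire, for a secondary outcome. As printed, question 16 cannot separate knowledge from agreement, and an all-'yes' pupil looks fully informed. That follows from the items and the taught messages alone, under any key that follows those messages.

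The size and sign of the bias depend on g, which the documents do not give. With equal g, a 30-point difference becomes 15 at g = 0.5 and 6 at g = 0.8. With g of 0.5 in control and 0.8 in intervention, and no true difference, an apparent 18 points arises. Whether a real gain would be missed depends on its true size: the 30-point example would probably still be detected at g = 0.8, while a 10-point gain could well be lost. The change is worth making because it is cheap and can only be made before the data are collected.

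**What to change.** At the questionnaire pretest that the Activity Plan (section 6.0) already includes, before baseline:

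1. Add to question 16 some false statements about tooth decay whose correct answer is 'no'.
2. Give every item an 'I don't know' answer, counted as not correct.
3. Score knowledge over true and false items together. With four true and F false items, an all-'yes' pupil scores 4/(4 + F): 67% with two false items, 50% with four, and no longer 100%. The share of 'yes' on the false items, by arm, also shows whether yes-saying differs between the arms.
4. Preferably split 16.3 into its three elements (fluoride paste, brushing twice daily, not rinsing), because one yes/no on all three cannot be interpreted for a pupil who knows only some of them.

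The cost is a questionnaire edit and a slightly longer form. No extra participants, visits or staff are needed.

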### **Adolescent's oral health knowledge and related behaviours**

The proportion of adolescents with knowledge on sugar containing food as a cause of tooth decay is reported to range from 50-86.5% in Europe and America (Smyth et al., 2007, Graça et al., 2019), 27.5-69.4% in Asia (Lian et al., 2010, Dixit et al., 2013, Hague et al., 2016) and 48.2%-94.6% in Africa (Oredugba et al., 2004, Mashoto et al., 2009, Okemwa et al., 2010, Mbawala et al., 2010, Nyamuryekung'e, 2012). The proportion of those with knowledge on the importance of regular tooth brushing ranges from 19-98.1% in all regions (Oredugba et al., 2004, Shenoy et al., 2010, Dixit et al., 2013, Hague et al., 2016, Graça et al., 2019). It is 33-71% in Europe and America (Smyth et al., 2007, Graça et al., 2019), 19.0-57.4% in Asia (Lian et al., 2010, Shenoy et al., 2010, Dixit et al., 2013) and 65-98.1% in Africa (Darout et al., 2005, Carneiro et al., 2011, Varenne et al., 2006). Percentage of adolescents with knowledge on use of fluoridated toothpaste as a means of preventing dental caries ranged from 40.5-75.3% in Europe and America (Smyth et al., 2007, Graça et al., 2019), 18-83.7% in Asia (Lian et al., 2010, Dixit et al., 2013, Sanadhya et al., 2014, Hague et al., 2016) and 6-87.7% in Africa (Varenne et al., 2006, Carneiro et al., 2011, Elzahaf et al., 2019). Percentage of adolescents with knowledge on importance of dental check up at least once a year range as follows 35.4-50% in Europe and America (Smyth et al., 2007, Graça et al., 2019) and 42-98.1% in Asia and Africa (Blaggana et al., 2016, Al-Hussaini et al., 2003, Carneiro et al., 2011, Varenne et al., 2006)

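### Knowledge item 16.3 joins fluoride toothpaste, twice-daily brushing, spitting and not rinsing in one tick, so a difference on it cannot be attributed to knowledge of fluoride or of brushing for decay

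*Protocol*

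**What the plan says.** Appendix 1, Part 2, question 16 opens with "I can avoid tooth decay by accomplishing the following" and takes a yes or no for each of four items. Items 16.1 and 16.2 concern sugary foods and sugary drinks, and 16.4 concerns dental check-ups. Item 16.3 reads "Using fluoride toothpaste to brush my teeth at least twice a day spitting the foam but not rinsing it out".

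Question 17, on avoiding bleeding gums, has a separate brushing item, 17.2: "Brushing teeth for 2 minutes at least twice a day". Question 18 is about when to change a toothbrush. No other knowledge item mentions fluoride.

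Section 4.6 lists the messages that peer educators deliver every two weeks for 18 months. Message 2 is "Brush your teeth for 2 minutes ensuring all the surfaces are cleaned; twice per day in the morning and evening before retiring to bed". Message 3 is "Use fluoride toothpaste to brush, spit the foam but do not rinse it out".

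Objective 3 (Section 2.2) assesses the effect of the "modified basic package of oral care intervention on knowledge and behaviors related to dental caries after 18 and 24 months of follow up". Section 4.10 places knowledge second in rank: "The secondary outcomes include improved oral hygiene (plaque score) and oral health knowledge and related behaviors". Appendix 6 reports Objective 3 as numbers, percentages and odds ratios with 95% confidence intervals.

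**The concern.** Item 16.3 contains four elements: the paste contains fluoride, brushing is at least twice a day, the foam is spat out, and the mouth is not rinsed. One tick cannot show which of them a pupil accepts. A pupil who knows that fluoride toothpaste and twice-daily brushing prevent decay, but thinks one should rinse, cannot express that: a yes endorses a clause the pupil rejects, and a no hides two things the pupil knows.

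At stake is the interpretation of Objective 3. If the arms differ on 16.3, the report can say that agreement with the combined practice changed. It cannot say whether pupils learned about fluoride, about brushing frequency for decay, or only that they should not rinse.

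**Working it through.** The protocol states no figure on this point, so there is nothing to reproduce. The check is in three steps.

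**1. Is the information available elsewhere in the questionnaire?**

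| Knowledge | Item 16.3 | Anywhere else as knowledge? |
|---|---|---|
| Fluoride toothpaste, for decay | yes, joined | no |
| Brushing at least twice a day, for decay | yes, joined | no; 17.2 asks it for bleeding gums |
| Spitting the foam | yes, joined | no |
| Not rinsing | yes, joined | no |

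Questions 21 and 24 to 26 ask about brushing frequency and toothpaste use separately, but these concern behaviour and the product used, not what the pupil believes prevents decay.

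The protocol elsewhere treats these as different quantities. Section 3.0 gives a separate range for "knowledge on use of fluoridated toothpaste as a means of preventing dental caries" (6 to 87.7% in Africa) and for knowledge of regular brushing (65 to 98.1% in Africa). It also reports gains after education separately: 46 to 100% for brushing and 31.5 to 52.2% for fluoride toothpaste. Item 16.3 yields a figure comparable with neither.

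**2. How much does one tick lose?** Four yes/no elements give 2 × 2 × 2 × 2 = 16 belief patterns, which map to 2 answers.
- If a pupil ticks yes only when agreeing with all four, 1 pattern gives yes and 15 give no.
- If agreeing with any one is enough, 15 give yes and 1 gives no.

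The item does not tell pupils which rule to use.

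**3. Can one observed change have different causes?** This is an illustration only. Assumed: the four elements are independent, pupils tick yes only if they accept all four, and starting knowledge is fluoride 0.60, twice a day 0.80, spitting 0.70, no rinsing 0.50. The documents give no values for spitting or rinsing.

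P(yes) = fluoride × twice a day × spitting × no rinsing.

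- Start: 0.60 × 0.80 × 0.70 × 0.50 = 0.168
- Only fluoride knowledge rises, to 0.90: 0.90 × 0.80 × 0.70 × 0.50 = 0.252
- Only no-rinse knowledge rises, to 0.75: 0.60 × 0.80 × 0.70 × 0.75 = 0.252
- Twice a day rises to 1.00 and spitting to 0.84, fluoride unchanged: 0.60 × 1.00 × 0.84 × 0.50 = 0.252

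Each route gives the same odds ratio, (0.252/0.748) / (0.168/0.832) = 0.337/0.202 = 1.67. In the second and third routes fluoride knowledge has not moved at all. If pupils answered on the fluoride part alone, those two routes would give 0.60 against 0.60, an odds ratio of 1.0.

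**The case against.** The best defence is that 16.3 measures what is taught. Message 3 itself joins fluoride, spitting and not rinsing; only brushing frequency comes from message 2. The item can therefore be read as a test of whether the whole practice is known, and it could enter a total knowledge score on that basis. Objective 3 and Section 4.10 speak of knowledge in aggregate, and Appendix 6 does not name fluoride or brushing knowledge as separate endpoints. The separate percentages in Section 3.0 describe other studies and commit this trial to nothing. All of this stands. It supports a statement about the combined practice but none about its parts. A scoring rule in an analysis plan would not help either, since no rule can separate elements collected in one tick.

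Two stronger readings are tempting and should be set aside.

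- A reader might infer that the comparison of arms is biased, because control pupils may never have met the no-rinse advice. The documents do not support that. Not rinsing is part of message 3, so a gain on that clause is a real effect of the intervention on caries-related knowledge. The fault is one of attribution within the item.
- A reader might infer that brushing knowledge goes unmeasured. Item 17.2 asks about twice-daily brushing without a fluoride or rinsing clause. It sits under the bleeding-gums stem, so the gap is limited to brushing for decay. For fluoride the gap is complete.

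**Conclusion.** The point holds in limited form. That 16.3 combines four elements, and that no other knowledge item covers fluoride or brushing for decay, is read directly from the questionnaire and needs no assumption. A difference between arms on 16.3 can be reported as a change in agreement with the combined practice, and not as a change in knowledge of fluoride or of brushing for decay.

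The size of the problem cannot be derived from the documents. The rise from 16.8% to 25.2% (odds ratio 1.67) rests on assumed knowledge levels, independence and strict all-parts answering. It shows that the ambiguity is possible, not how large it will be.

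The consequence is confined to one item of a secondary outcome. Caries status, gingivitis, oral health related quality of life and the sample size of 1760 are unaffected, and the brushing and fluoride-toothpaste behaviours under Objective 3 have their own questions. This is a cheap improvement worth making, and not a threat to the trial.

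**What to change.** Before baseline, replace 16.3 with three yes/no items under the existing tooth-decay stem:

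- (a) brushing with toothpaste that contains fluoride;
- (b) brushing at least twice a day;
- (c) not rinsing after spitting out the foam.

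Use the same wording at baseline and at every follow-up, and report each as its own proportion, with its own odds ratio, under Objective 3. The questionnaire pretesting listed in the Activity Plan (Section 6.0) is a natural place to try the wording.

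The cost is two extra lines (three items in place of one). If baseline has already been collected, keep 16.3 for continuity and add the three items beside it. They will then have no baseline value and can be compared between arms at follow-up only.

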Basic Package of Oral Health Care (BPOC) is an intervention recommended by the World Health Organization (WHO) as an affordable and effective preventive and curative modality of oral diseases in developing countries (Batra *et al.*, 2014). The intervention comprises of three components; Oral Urgent Treatment (OUT), Atraumatic Restorative Treatment (ART) and Affordable Fluoride Toothpastes (AFT). Safety and how well the components of the intervention works have been proved in previous studies (Kikwilu *et al.*, 2009; Mashoto *et al.*, 2010), however effectiveness and implementation of the strategy as a package has not been tested in most African countries including Zambia. Modification of the conventional BPOC in this study entail inclusion of oral health education and provision of fluoridated tooth pastes to

encourage use of the oral care products in future. The conventional BPOC make fluoride tooth pastes available and affordable through regulating policies such as reduction or eliminating tax to the products aiming at reducing their market price. This is a level three trial that aims at assessing the effectiveness of the modified BPOC in improving oral health-related behaviors, oral health and related quality of life.

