##### **4.9.2.1. Oral health related behaviors**

Adolescents will be requested to report their oral health related behaviors. In respect to tooth brushing, use of fluoridated tooth paste and sugar consumption they will be required to reflect their conduct in the past 30 days. Frequency of tooth brushing per day and use of fluoridated toothpaste will be assessed and recoded using a 4-point scale follows {1= I didn't, 2= I did but not every day, 3=I did once a day, 4 = I did twice a day or more}. Intake of sugar containing drinks or foods will be assessed and recorded using a 5-point scale as follows {1= I didn't take, 2= occasionally per week, 3= Once per day, 4= Twice to four times per day, 5 = Five times or more per day}. Visiting a dentist in past one year for checkup will be assessed and recorded based on a 3-point scale {1= I didn't attend, 2= I attended once, 3=I attended twice or more}

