##### **Mitigation**

- 1 Dental caries assessment using CAST (Frencken *et al.*, 2011) will be used to capture incremental stages of dental caries development and dental caries variable will continue being followed up after 24 months.
- 2 The data analyst will be blinded during analysis stage to avoid subjective decisions on handling missing data, transforming variables, undertaking subgroup analysis, and selecting covariates due to prior knowledge of treatment allocation.
- 3 The interventions will end six months before the last follow up and therefore the effect of adolescents acting due to the reason that their being followed-up will be controlled in the data collected at the last follow up visit.

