| 3. Chewing stick       |  |
| 4. Plastic tooth brush |  |

23. If you use a plastic tooth brush how often do you change it?

- |                                  |                          |
|----------------------------------|--------------------------|
| 1. After 1 month                 |  |
| 2. After 2 months                |  |
| 3. After 3 months                |  |
| 4. When worn out (bristles bent) |  |

24. Do you use toothpastes for tooth brushing?

- |        |                          |
|--------|--------------------------|
| 1. No  |  |
| 2. Yes |  |

25. If you do, does the tooth paste contain fluoride

- |                 |                          |
|-----------------|--------------------------|
| 1. No           |  |
| 2. Yes          |  |
| 3. I don't know |                          |

26. How often did you use fluoridated toothpaste during the past 30 days?

- |                               |                          |
|-------------------------------|--------------------------|
| 1. I didn't use tooth paste   |  |
| 2. I used but not everyday    |  |
| 3. I used once a day          |  |
| 4. I used twice a day or more |  |

27. How many times did you attend for dental checkup in past 1 year?

1. I did not attend
2. I attended once
3. I attended twice or more

|  |
|--|
|  |
|  |
|  |

28. If you did not attend for check up, what is the reason?

1. I did not have any problem
2. My parents didn't have money
3. My parents didn't have time
4. The clinic is very far
5. I had fear of a dentist
6. I used traditional medicine
7. Others Specify .....

|  |
|--|
|  |
|  |
|  |
|  |
|  |
|  |

29. Did you experience any of the following dental problems in the past 3 months?

- |                          | 1=yes                    | 2=no                     |
|--------------------------|--------------------------|--------------------------|
| 1. Painful tooth         |  |  |
| 2. Painful gums          |  |  |
| 3. Swollen gums          |  |  |

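### The fluoride-toothpaste item (question 26) has no true answer for users of paste with no or unknown fluoride, and no item records whether the paste came from the study

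*Protocol*

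**What the plan says.** Section 4.11.2 lists use of fluoride toothpaste among the dependent variables, and section 4.10 gives its rank: "The secondary outcomes include improved oral hygiene (plaque score) and oral health knowledge and related behaviors". Section 4.9.2.1 sets a four-point frequency scale over the past 30 days, starting "1= I didn't, 2= I did but not every day, 3=I did once a day".

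Appendix 1 has three items on paste:
- Question 24 asks whether toothpaste is used.
- Question 25 asks "If you do, does the tooth paste contain fluoride", with answers for no, yes and not knowing.
- Question 26 asks "How often did you use fluoridated toothpaste during the past 30 days". It is the only item that puts fluoride paste on the section 4.9.2.1 scale, and its code 1 reads "I didn't use tooth paste".

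The intervention arm gets paste by "providing 250g pack of fluoride toothpaste every two months and toothbrushes every three months for 18 months" (section 4.6), and Table 1 shows nine sessions, the last in months 17-18. The stated aim of giving paste is to "encourage use of the oral care products in future" (section 1.1). Section 2.2 assesses behaviours at 18 and 24 months. Section 4.14, mitigation 3, says "The interventions will end six months before the last follow up" and uses that gap against pupils acting because they are being followed up.

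**The concern.** The stem of question 26 is about fluoridated paste, but its negative answer denies any paste. A pupil who brushes daily with non-fluoride paste, or with paste of unknown content, must either tick a frequency and be coded as a fluoride user, or tick code 1 and be coded as using no paste. Both are false.

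The error need not be the same in the two arms. Only intervention pupils are handed fluoride paste and hear the fluoride message every two weeks (section 4.6), and participants know their group (section 4.9.2). What a pupil knows about fluoride content therefore differs by arm by design.

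A second gap is that nothing in the questionnaire says whose paste was used. At month 24 the protocol looks at behaviour six months after supply stops. If study paste is still in the home, continued use of it and use of paste obtained otherwise give the same answer. No later analysis plan can recover data that were not collected.

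**Working it through.** **1. Questionnaire against protocol body**

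| Pupil's paste | Question 25 | Question 26 as printed | Scale in section 4.9.2.1 |
|---|---|---|---|
| Fluoride | yes | codes 2-4, true | codes 2-4, true |
| None used | not asked | code 1, true | code 1, true |
| Non-fluoride | no | no true answer | code 1, true |
| Unknown content | don't know | no true answer | no certain answer |

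The wording in section 4.9.2.1 covers the non-fluoride user; the printed item does not. Neither covers unknown content.

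**2. Direction of the error (illustration only)**

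The literature review (section 3.0) gives 38.9% to 81.3% use of fluoridated paste in African studies. The shares below are assumed; the protocol does not give them.

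- *Undercounting in controls.* Let true use p be equal in both arms, and let a share u of control users not know the content and go uncounted. Observed control use is p(1 - u), and the false odds ratio is [p/(1 - p)] / [p(1 - u)/(1 - p(1 - u))]. At p = 0.389, u = 0.1 gives 1.18 and u = 0.3 gives 1.70. At p = 0.813 the same shares give 1.59 and 3.29.
- *Overcounting in controls.* Let a share v of control pupils who do not use fluoride paste use another paste and tick a frequency. Observed use is p + v(1 - p). At p = 0.389 and v = 0.3 this is 0.389 + 0.3 x 0.611 = 0.572, so a true arm difference would shrink.

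The bias can go either way.

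**3. Quantity supplied**

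18 months / 2 months = 9 distributions, which reproduces the nine sessions in Table 1. 9 x 250 g = 2,250 g per participant.

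**4. How long it can last**

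Assumptions not in the protocol: g grams per brushing, twice daily, one user, 30.44 days per month.

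- Used by month 18: 18 x 30.44 x 2 x g = about 1,096g grams.
- Months left after month 18: (2,250 - 1,096g) / (60.9g).

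| g per brushing | Left at month 18 | Further months |
|---|---|---|
| 1.0 g | 1,154 g | 19.0 |
| 1.5 g | 606 g | 6.6 |
| 2.0 g | 58 g | 0.5 |

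- Stock lasts to month 24 if g <= 2,250 / (24 x 30.44 x 2) = 2,250 / 1,461 = 1.54 g.
- Stock reaches the start of the 30-day recall window, about month 23, if g <= 2,250 / 1,400 = 1.61 g.
- With sharing, the 1.54 g limit falls to 0.77 g for two equal users and 0.31 g for five. Once-daily brushing doubles it.
- The budget's 570 dozen packs (6,840), spread over an assumed 880 pupils (half of 1,760), give 7.8 packs each. That is about 1,943 g and a limit of 1.33 g.

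**5. Conflicting inputs**

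The intervention is called six months in section 2.2, paste supply runs for 18 months in section 4.6, and section 4.6.2 refers to 24 months. The pack is 250 g in section 4.6 and 250 mg in the budget. The calculation uses section 4.6 and Table 1; on the other figures it changes greatly.

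**The case against.** The strongest reply has five parts.

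- *Question 25 already records non-fluoride and unknown content, and combining it with question 26 is a scoring rule that a statistical analysis plan may hold.* This stands in part. It would be wrong to infer that the questionnaire ignores unknown content, and the lack of a scoring rule is not the point here. But question 26 still forces a false answer and contradicts section 4.9.2.1. Any rule built on question 25 would also depend on pupil knowledge, which differs by arm.
- *Use of supplied paste at month 18 is an intended effect of the package.* This stands. A reader might infer that the item measures only being told and supplied. The protocol does not support that: the outcome is use of fluoridated paste, and supply is part of the intervention.
- *Section 4.14 does not claim that study paste is gone by month 24.* This stands. The six-month gap is offered against observation effects, not as a washout of paste.
- *Carry-over is not shown.* This stands. Grams per brushing and sharing are not given, and pupils live in families whose size the protocol itself records.
- *Redefining the month-24 outcome as family-obtained paste would be worse.* This stands. It would score an intervention pupil using leftover fluoride paste as a failure, a penalty that controls cannot incur. A paste-source answer also reveals the arm, against the planned blinding of the analyst.

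**Conclusion.** Two limited points hold. First, code 1 of question 26 contradicts section 4.9.2.1 and leaves users of non-fluoride or unknown paste without a true answer. The misclassification can differ by arm, but neither its size nor its direction follows from the protocol; the odds ratios above only illustrate assumed shares. Second, paste source is not recorded, so the month-24 value cannot separate leftover study paste from other paste.

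Leftover paste at month 24 is possible at up to about 1.54 g per brushing, on 9 x 250 g, twice daily and no sharing, and at proportionally less if shared. At 2 g per brushing it is gone soon after month 18. A reader might infer that a month-24 arm difference would be carry-over; the documents do not show that.

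The item belongs to a secondary outcome. The primary outcomes and the sample size are not affected. The change is still worth making, because it is cheap and the missing data cannot be recovered later.

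**What to change.** - Reword code 1 of question 26 to say that no *fluoridated* toothpaste was used, in line with section 4.9.2.1.
- Add an answer for toothpaste of unknown fluoride content.
- Record the brand, so that the team codes fluoride content in the same way in both arms.
- At months 18 and 24, ask whether the paste used in the past 30 days came from the study or elsewhere. Use this as a descriptive or sensitivity item only, and keep it from the blinded analyst until the main analysis is done.
- Keep the outcome as use of fluoridated toothpaste at both times.
- Reconcile sections 2.2, 4.6 and 4.6.2 on intervention length, and section 4.6 with the budget on pack size. No change to what is supplied is proposed.

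Cost: a slightly longer questionnaire, brand coding, and separate handling of the source item. Sample size and visit schedule do not change.
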